**abbreviated table**

| acronym | formal name |
| --- | --- |
| ALP | Alkaline phosphatase |
| ALT | Alanine aminotransferase |
| AST | Aspartate aminotransferase |
| BS | Bristol Stool |
| CSBM | Complete Spontaneous Bowel Movements |
| CK | Creatinekinase |
| Cl | chlorine |
| CSS | Constipation Scoring System |
| EOT | End of treatment |
| EDC | Electronic data capture |
| EMA | European Medicines Agency |
| eCRF | electronic case report form |
| FAS | full analysis set |
| jRCT | Japan Registry of Clinical Trials |
| gamma-GTP | Gamma-glutamyl transpeptidase |
| HDL | High density lipoprotein |
| IBAT/ASBT | Ileal bile acid transporter/ apical sodium-dependent bile acid transporter |
| PAC-QOL | Patient assessment of constipation quality of life |
| k | potassium |
| LDL | Low density lipoprotein |
| Na | sodium |
| PPS | per protocol set |
| quality of life | Quality of life |
| Rome IV | -. |
| SBM | Spontaneous Bowel Movements |
| SAS | safety analysis set |

# **0. Overview**

| Study title | Efficacy of elobixibat for recovery of loss of defecation desire in patients with chronic constipation. Multicenter, single-group, open label study. |
| --- | --- |
| Name of study drug | Elobixibat 5mg |
| Target disease | chronic constipation |
| Research Methods, Research Design | A multicenter, single-arm, open-label, before-and-after study |
| research period | Registration period: from the date of jRCT publication (date of notification by the Minister of Health, Labour and Welfare) to July 31, 2022  Study period: From the date of publication of the jRCT (date of notification to the Minister of Health, Labour and Welfare) to March 31, 2023 (approximately 2 years)  Planned duration of subject participation: up to 9 weeks from obtaining consent  Observation period: 2~4 weeks  Treatment period: 4 weeks (maximum 5 weeks) |
| Research implementation plan № | R-LODD study |
| purpose | Patients of chronic constipation without defecation desire will be orally administered elobixibat 10 mg once daily before meals for 4 weeks. The primary endpoint of the pre/post comparative study will be the percentage of improvement in loss of defecation desire from Week 2 of the observation period at Week 4 of the treatment period. |
| Target number of subjects | 40 cases (as this registration case) |
| inclusion criteria | **selection criteria**  Patients who meet all of the following   - at the time of provisional registration  1. Patients diagnosed with chronic constipation according to the Rome IV criteria for the diagnosis of chronic constipation 2. Age: 20 years or older (at the time of obtaining consent) 3. Gender: Any 4. outpatients 5. Patients for whom written consent can be obtained 6. Patients who can record defecation, etc. in the patient diary   At the time of registration: Dosing start criteria  Patients with the following  "loss of defecation desire*" in the second week of the observation period (1 week before the start of the treatment period) *  *" loss of defecation desire " refers to patients whose "presence or absence of defecation desire " on the patient questionnaire was "4. almost never” or “5. never".  **Exclusion criteria**  **At the time of temporary registration**  Exclude patients with any of the following conditions   1. Patients with organ-related constipation or suspected of having organ-related constipation 2. Patients with or suspected of having functional ileus 3. Patients with or suspected of having inguinal hernia 4. Patients with a history of open abdominal surgery within 12 weeks prior to obtaining consent (excluding appendicitis resection) 5. Patients with a history of surgical or endoscopic procedures related to gallbladder resection and papillotomy 6. Patients with complications of malignancy   However, patients who have undergone radical surgery or who have completed chemotherapy or radiotherapy may be registered.   1. Pregnant women, lactating women, women who may be currently pregnant, or patients who cannot give consent to use contraception while participating in the study 2. Patients with serious renal, hepatic, or cardiac disease 3. Patients with drug allergy to the study drug 4. Patients who are participating in other clinical studies, or who have participated in other clinical studies within 4 weeks prior to obtaining consent   However, observational studies are excluded.   1. Other patients who are judged by the principal investigator or sub-investigator to be inappropriate for this study.   At the time of registration: Dosing start criteria  (1) Patients who increased the dose of concomitantly restricted drugs during the observation period  (2) Patients who used concomitantly prohibited drugs during the observation period |
| Name and dosage of the study drug | Elobixibat  Dose: Start with 10 mg (2 tablets) of elobixibat, and then can be increased or decreased (5 mg or 15 mg) according to symptoms. |
| Method of administration, observation and duration of administration | The study will consist of a 2-week observation period and a 4-week treatment period.  During the treatment phase, the study drug is administered orally once daily before meals for 4 weeks. |
| evaluation item | **Effectiveness**  Primary endpoint.  Percentage of improvement in loss of defecation desire in the fourth week of the treatment period from the second week of the observation period (patient questionnaire)  Secondary endpoints: The following items will be evaluated and their relevance will be examined.  (1) Changes in the following items in each week of the treatment period and comparison of Week 4 of the treatment period with Week 2 of the observation period   1. Presence of defecation desire: patient questionnaire 2. Satisfaction with defecation desire: a patient questionnaire 3. Satisfaction with straining: patient questionnaire 4. Degree of straining: patient diary 5. Presence of a sense of incomplete evacuation: patient diary 6. Satisfaction with treatment: patient questionnaire 7. Spontaneous bowel movement (SBM) frequency 8. Complete Spontaneous Bowel Movement (CSBM) frequency 9. Stool hardness based on the Bristol Stool Form Scale     (2) Comparison of the following items at Week 4 of the treatment period with Week 2 of the observation period  1. Constipation score: CSS  2. JPAC-QOL score  3. absolute value and percent composition of bile acid concentration in feces  (3) Changes in the time from taking elobixibat to defecation each week during the treatment period  (4) Consideration of the relationship between the evaluation items  **safety**  Incidence rate of diseases, etc. |
| contact information (for inquiries) (e.g. corporate phone number) | Principal Investigator: Department of Palliative Medicine, Yokohama City University Hospital  [name]  [contact] (representative)  Research secretariat: Yokohama City University Hospital  Next Generation Clinical Research Center  　　　[name] [name]  [contact] [contact] |
| Rules and Regulations to be observed | All persons involved in this research will conduct it in accordance with the "Clinical Research Act", the "Enforcement Regulations of the said Act and other related notifications", in accordance with the "Declaration of Helsinki of the World Medical Association", which all medical research involving human subjects should comply with. |

# **1. Purpose of this study**

Patients with chronic constipation will be orally administered elobixibat 10 mg once daily before meals for 4 weeks. A before-and-after study will be conducted, and the rate of improvement in loss of defecation desire from the second week of the observation period in the fourth week of the treatment period will be the primary endpoint.

# **2. background and scientific rationale for the study design**

Elobixibat specifically inhibits IBAT/ASBT (ileal bile acid transporter/apical sodium-dependent bile acid transporter), which is a transporter involved in the reabsorption of bile acids at the terminal ileum [1]. It was approved for the treatment of chronic constipation in Japan in January 2018. It is thought that the IBAT inhibitory action of elobixibat increases the amount of bile acids reaching the colon by inhibiting bile acid reabsorption, thereby promoting water secretion into the lumen of the large intestine and gastrointestinal motility. In addition, bile acids are expected to have a restorative effect on defecation desire because they have an effect to lower the rectal sensory threshold, which is an objective index of defecation desire [2,3].

In 2020, a web-based questionnaire-based survey conducted at Yokohama City University reported that patients with chronic constipation had a significantly higher rate of loss of defecation desire than healthy adults, with about 60% of patients losing their defecation desire [4]. Patients whose defecation desire were improved by treatment had higher treatment satisfaction than those whose defecation desire were not improved [4], suggesting that the presence or absence of bowel movements in the treatment environment is related to treatment satisfaction and the importance of defecation desire in the treatment of constipation. However, in actual clinical practice, it has not been investigated whether elobixibat, which increases bile acids in the colon, has a restorative effect on defecation desire and how long it takes for recovery.

In a double-blind, placebo-controlled, 2-week study, elobixibat improved various symptoms in Japanese patients with chronic constipation, such as the number of spontaneous bowel movements (SBM), the number of complete spontaneous bowel movements (CSBM), the time to the first spontaneous bowel movement, and stool hardness, [5]. Safety and efficacy have also been confirmed in a single-arm study without a control group for 52 weeks [5]. None of these studies examined recovery of defecation desire.

In this study, we will investigate the improvement rate of defecation desire and symptoms of defecation difficulty in patients with chronic constipation, based on the improvement rate of bowel movements after 4 weeks of treatment with elobixibat.

## 2.1 Target diseases

Chronic constipation is a frequent functional disorder encountered in daily clinical practice with a prevalence of 2-27% in Japan. It is more common in women than in men, and its prevalence increases with age in both sexes [6]. In addition, a decrease in quality of life (QOL) has been reported, including a significant decrease in daily activity and work productivity compared to patients without chronic constipation [7]. In addition, many patients with chronic constipation are said to be less satisfied with conventional treatment methods, and it has been reported that they have more subjective symptoms such as abdominal distension and dyspepsia as well as frequency of defecation and hardness of stool [8].

Understanding the unpleasant symptoms of this "difficulty" and improving constipation symptoms, including recovery of defecation desire, will lead to an increase in QOL.

## 2.2. Standard treatment

2.2.1 History of the standard treatment that has been implemented so far, etc.

Pharmacotherapy with laxatives is commonly used for chronic constipation in which symptoms do not improve sufficiently despite guidance on diet, lifestyle, and defecation habits. Two types of laxatives, magnesium oxide and stimulant laxatives, are widely used in clinical practice. Magnesium oxide is the most commonly prescribed drug, and regular monitoring of serum magnesium concentration is necessary for use in elderly patients and patients with impaired renal function such as those with chronic kidney disease.

On the other hand, although stimulant laxatives have powerful effects, they should be used only as a general rule, because of concerns about dependence and drug resistance due to continuous use. Magnesium oxide, which can be finely adjusted in dose and is highly safe, is therefore used as the first-line drug. However, as mentioned above, there is a risk of hypermagnesemia not only in patients with impaired renal function and patients taking long-term high doses, but also in rare cases with normal renal function. Therefore, it is recommended to monitor serum magnesium levels at 3-6 month intervals during long-term use [9].

2.2.2 Current standard of care

Pharmacotherapy for chronic constipation is considered to be one of the standard treatments for constipation along with dietary guidance and lifestyle guidance. However, as mentioned above, there are problems such as side effects and tolerance / addiction during long-term use for various drugs that are the first choice [10-12].

In recent years, the number of drugs for the treatment of chronic constipation has increased due to the emergence of linaclotide and lubiprostone preparations with a high level of evidence. In addition, the Ministry of Health, Labour and Welfare (MHLW) has issued five preparations, linaclotide, lubiprostone, elobixibat hydrate, macrogol 4000 combination, and lactulose, for use in patients with inadequate efficacy of existing constipation medications [13,14]. The treatment situation has changed significantly.

## 2.3. Study treatment

The study drug elobixibat was approved for the manufacture and sale as a treatment for chronic constipation (excluding constipation due to organic disease) in January 2018. By inhibiting the bile acid reabsorption transporter in the terminal ileum, elobixibat increases bile acids in the colon and promotes water and electrolyte secretion as well as gastrointestinal motility. Since Clozapine is only slightly absorbed into the body and does not enter the bloodstream to exert its effects, there is little concern about drug interactions with concomitant medications.

As risks of the study treatment, abdominal pain and diarrhea are described in the package insert as the main adverse reactions. In a domestic clinical study of 631 patients with chronic constipation, adverse drug reactions including abnormal laboratory values occurred in 292 (46.3%) patients, and the major adverse drug reactions were abdominal pain in 120 (19.0%) patients and diarrhea in 99 (15.7%) patients.

As a benefit of the study treatment, the percentage of improvement in defecation desire after 4 weeks of treatment will lead to the confirmation of recovery of defecation desire and the improvement of symptoms of dysuria, which will lead to the improvement of QOL and treatment satisfaction.

## 2.4. Study design and primary endpoints

This was a multicenter, single-arm, open-label, before-and-after study in patients with chronic constipation.

[Primary endpoint] Percent improvement in loss of defecation desire from Week 2 of the observation period at Week 4 of the treatment period (patient questionnaire)

[Basis for setting]

The EMA guideline states that it is important to assess quality of life [15], and a web-based questionnaire survey in 2020 reported that patients with chronic constipation had a higher rate of loss of defecation desire than healthy adults, and that patients whose defecation desire improved with treatment had a higher level of treatment satisfaction [4]. We hypothesize that elobixibat increases the amount of bile acids that enter the lumen of the large intestine, and that these bile acids lower the rectal sensory threshold, which leads to the recognition of defecation desire.

In this study, "confirmation of recovery of loss of defecation desire ", which is considered to be related to treatment satisfaction, was the primary endpoint.

In the previous literature [5], improvement in the number of spontaneous bowel movements, etc., was observed after 2 weeks of treatment, and since elobixibat is effective in improving constipation at an early stage, we believe that early recovery of bowel movements can be expected in actual clinical practice. In this study, we set "confirmation of recovery of defecation desire " at 4-week administration, which is the usual interval between visits.

## 2.5 Significance of this study

The primary endpoint of the study was "confirmation of recovery of loss of defecation desire ".

# **3. Study drug information**

## 3.1. Study drug

Generic name: Elobixibat hydrate

Product name: Goofis® Tablets 5mg

Storage method: room temperature storage

Name of manufacturing and marketing company: EA Pharma Co.

Indications: Chronic constipation (excluding constipation caused by organic diseases)

Dosage and Administration (Method of Use): The usual adult dosage of elobixibat is 10 mg orally once daily before meals. The dosage may be adjusted according to symptoms, but the maximum dosage is 15 mg per day.

*Formulation* (appearance): Pale yellow, circular, film-coated tablets

## 3.2 Management of study drugs

The study drug will be Goofis® Tablets 5 mg. Refer to the attached document for prescription and administration.

## 3.3 Ensuring the quality of study drugs

Refer to the attached document to ensure quality.

# **4. Criteria and definitions used in this study**

|  | (data) Item | Contents | Appendix / Patient diary |
| --- | --- | --- | --- |
| Criteria | Diagnosis of chronic constipation | Diagnostic criteria for functional constipation in Rome IV (Drossman, DA. Hasler, WL. Gastroenterology. 2016; 150: 1257-1261.) | Appendix E |
| definition | Spontaneous bowel movement (SBM) | Defecation that occurs without transanal laxative, enema or disimpaction: The number of "defecation that occurs without suppository, enema or disimpaction" in 7 days. Defecation within 24 hours after using a suppository or enema and defecation during disimpaction are not counted in the "number of spontaneous defecations". | Patient diary |
| definition | Complete Spontaneous Bowel Movement (CSBM) | Defecation occurring without residual sensation and without transanal laxatives/enema or removal of stool | Patient diary |
| Criteria | Satisfaction with defecation desire, bearing down, and treatment | On a scale of one to five.  1. very satisfied, 2. somewhat satisfied, 3. average  4. somewhat dissatisfied, 5. very dissatisfied | Appendix A: Patient Questionnaire |
|  | Defecation desire | On a scale of one to five.  1. always available, 2. usually available, 3. a little, 4. hardly, 5. not at all | Appendix A: Patient Questionnaire  Patient diary |
|  | Bearing down to defecate | On a scale of one to five.  1. Not pushing at all, 2. pushing a little, 3. Pushing to some extent, 4. Pushing hard, 5. pushes very hard | Patient diary |
|  | Symptom severity of constipation | Constipation Score (CSS):.  Evaluation of 8 items (frequency of defecation, difficulty in defecation, feeling of residual defecation, abdominal pain, time required for defecation, presence or absence of assistance in defecation, number of times when stool was not passed even after going to the toilet/24 hours, duration of illness with defecation disorder: year) on a 30-point scale | Appendix B |
|  | Classification of stool properties | Bristol Stool Shape Scale (BS Score): a global standard for assessing stool properties. 7-point scale for each bowel movement | Appendix C |
|  | QOL assessment | The Patient Assessment of Constipation Quality of Life (JPAC-QOL): A Disease-Specific Quality of Life Rating Scale for Chronic Constipation | Appendix D |

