6.5.2. Concomitant medications/adjunct therapy

6.5.2.1 Restricted Concomitant Drugs and Therapies: Observation Period to End of Treatment Period (Final Dose)

Chronic constipation medications (including over-the-counter medications, supplements, etc.) and therapies used prior to enrollment should not be changed in principle until the end of the treatment period. However, dose reduction or discontinuation is acceptable. The use of enemas, suppositories, and stool extraction is permitted only when adequate defecation is not observed.

6.5.2.2 Concomitant medications prohibited: from observation period to end of treatment period (last dose)

The use of the following drugs, which may affect this study, is prohibited.

Bile acid transporter inhibitors other than study drugs

Bile acid preparations (ursodeoxycholic acid, kenodeoxycholic acid, dehydrocholic acid)

Antacids containing aluminum (sucralfate hydrate, aldioxa, etc.)

Cholestyramine, Cholestymid

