Summary statistics will be obtained for the number of SBMs during the 7-day period (total number of SBMs during the 7-day period) at each week of the treatment period, and the corresponding t-test will be performed for the change in the number of SBMs during Week 4 of the treatment period from Week 2 of the observation period.

8. Complete spontaneous bowel movement (CSBM) frequency

Summary statistics will be obtained for the number of CSBMs during the 7-day period (total number of CSBMs during the 7-day period), and corresponding t-tests will be performed for the change in the number of CSBMs during Week 4 of the treatment period from Week 2 of the observation period.

9. Fecal hardness based on the Bristol stool form scale

Summary statistics of fecal hardness at each week of the treatment period will be calculated and compared with the second week of the observation period by the Wilcoxon signed rank test for the fourth week of the treatment period.

(2) Comparison of the fourth week of the treatment period with the second week of the observation period

1. Constipation Score (CSS)

Summary statistics will be calculated for the total constipation score and compared using the Wilcoxon signed rank test. Summary statistics are also calculated for each symptom and compared by Wilcoxon signed rank test.

2. JPAC-QOL score

Corresponding t-test for change in JPAC-QOL score.

3. Comparison of absolute values and percent composition of bile acid concentrations in feces

Corresponding t-test is performed for the change in bile acid concentration.

(3) Time from taking elobixibat to defecation in each week of the treatment period.

Summary statistics were calculated for the time from elobixibat administration to the first bowel movement in 7 days (median of 7 days) at each week of the treatment period, and the trends were examined.

(4) Examining the relationship between the evaluation items

To examine the relationship between the endpoints such as improvement of loss of defecation desire, patient satisfaction, and bile acid concentration.

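### Dose-to-defecation time in 16.3.2 (3) runs to the first bowel movement of any kind, so a movement produced by permitted rescue counts as the drug's time to effect

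*Protocol*

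**What the plan says.** Section 6.5.2.1 of the protocol governs the time from the observation period to the final dose. It states: "The use of enemas, suppositories, and stool extraction is permitted only when adequate defecation is not observed".

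Section 4 defines an SBM in two steps. The lead phrase is "Defecation that occurs without transanal laxative, enema or disimpaction". An operational rule follows: "Defecation within 24 hours after using a suppository or enema and defecation during disimpaction are not counted" in the number of spontaneous defecations. The next row defines a CSBM as "Defecation occurring without residual sensation and without transanal laxatives/enema or removal of stool", with no hour limit and no reference to the SBM row.

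Section 16.3.2 (1), items 7 and 8, analyses weekly totals of SBM and CSBM by name. Section 16.3.2 (3) then takes, for each treatment week, the "time from elobixibat administration to the first bowel movement in 7 days (median of 7 days", reports summary statistics and looks at trends. Section 9.2 lists the same endpoint and says only defecation.

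**The concern.** Rescue is used when defecation is inadequate, which includes days on which the tablet has not worked. If the clock stops at whatever movement comes first, such a day yields an ordinary-looking time to effect that was produced by the enema or suppository. The endpoint is meant to describe how soon after the tablet patients defecate. The study is open-label with a single arm, so no control group shows how often this happens. The section that defines the time already uses the terms SBM and CSBM for neighbouring endpoints, so the restriction was available and was not applied.

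**Working it through.** **1. The plan's own figure.** Section 16.3.2 (3) gives no figure. The only design figure is the power in 16.2: n = 37, null 20%, expected 45%, success at 13 or more. By the exact binomial, P(X ≥ 13 | 0.20) = 0.0231 and P(X ≥ 12 | 0.20) = 0.0517, so 13 is the right cut-off. P(X ≥ 13 | 0.45) = 0.916, which matches the stated 91.6%. This belongs to the questionnaire endpoint; nothing below enters it.

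**2. The definitions side by side.**

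| Endpoint | Rescue excluded? | 24-hour window stated? |
| --- | --- | --- |
| SBM (section 4) | yes | yes |
| CSBM (section 4) | yes | no |
| Dose-to-defecation time (16.3.2 (3)) | no | no |

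Only the last row carries no rescue exclusion at all.

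**3. Direction for one dose.** Let A be the time to the first movement of any kind and S the time to the first SBM. Every SBM is a bowel movement, so A ≤ S. Suppose there is no movement after a dose, a suppository or enema is used r hours after it, and a movement follows d hours later. As written, A = r + d. Under section 4 nothing counts as an SBM until r + 24 hours. With once-daily dosing that lies after the next dose, because r + 24 > 24 whenever r > 0. So S lies beyond the dosing interval, while the plan records the finite time r + d.

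**4. Effect on the weekly median.** The median of seven days is the fourth smallest value. Let s be the days whose first movement is an SBM and m the days whose first movement is produced by rescue. Rank days with neither as longer than the interval.
- Restricted to SBM, the weekly median is finite only if s ≥ 4.
- As written, it is finite if s + m ≥ 4.
- With s = 3 and m = 1, the first count is 3 (median beyond the interval) and the second is 4 (median finite).

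One rescue movement is enough to change that week's result.

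**5. Why the ranking is needed as well as the SBM restriction.** The protocol does not say how a day without a qualifying movement enters the median. If such days were left out once the endpoint was limited to SBMs, failed days would disappear instead of lengthening the time. To illustrate, assume movements occur independently on a proportion p of days, at times uniform on 1 to 20 h after dosing. Both inputs are assumed and no rescue is modelled. The true median is beyond the interval when at most 3 of 7 days have a movement:
- p = 0.4: 0.0280 + 0.1306 + 0.2613 + 0.2903 = 0.71
- p = 0.5: 0.50, by symmetry
- p = 0.6: 1 − 0.71 = 0.29

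The median over available days averages (1 + 20)/2 = 10.5 h in all three cases, so it would not distinguish them.

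**6. CSBM.** Take an invented week of five movements: one complete without rescue, one without rescue but with residual sensation, and three complete at 2, 20 and 30 h after a suppository. Under the 24-hour rule SBM = 3 (the two without rescue and the one at 30 h).
- If CSBM inherits the 24-hour rule, CSBM = 2.
- If rescue is attributed for 3 to 12 h, CSBM = 3.
- If it is attributed for 0 or 1 h, CSBM = 4.

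CSBM exceeds SBM only when the row's own rescue exclusion is given almost no duration.

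**The case against.** The strongest reply is that 16.3.2 leaves analysis details to a statistical analysis plan that is not shown. That stands for the scoring of days without a movement: the protocol states no cut-off at the next dose and no deletion of such days, so it cannot be faulted for dropping them. It does not stand for the event itself. The protocol fixes the event, and an analysis plan that follows it faithfully reproduces the problem, while one that restricts to SBM departs from it.

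A second reply is that the text is a loose translation. Section 16.3.1.1 even speaks of bowel movements where the primary endpoint is defecation desire. That looseness confuses movement with desire; it does not supply the word spontaneous, and 9.2 does not supply it either.

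A third reply, that the consequence is limited, is correct. The endpoint has no test and no pre-treatment comparator.

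A reader might also infer that CSBM counts include enema- or suppository-produced movements and can exceed SBM counts. The documents do not support this. The CSBM row excludes such movements in its own words, and its name, Complete Spontaneous Bowel Movement, naturally carries the SBM rule over. Only the length of the window is unstated.

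**Conclusion.** The time endpoint is defective as written: it can credit a rescue-produced movement to the drug, and for any dose the resulting time is never longer than the time to the first SBM. The average distortion cannot be given, because the documents contain no rescue frequency or timing. The two-against-one-interval comparison in a week with three SBM days and one rescue day shows that a single event can matter, provided days with no movement are ranked as longest. The shares 0.71, 0.50 and 0.29 and the 10.5 h average follow from assumed inputs without rescue. They support the ranking rule and do not measure the rescue error.

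The point concerns one secondary descriptive endpoint. The CSBM matter is a wording clarification. The primary endpoint and its 91.6% power are untouched.

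**What to change.** In 16.3.2 (3), and correspondingly in 9.2, define the time as running from each dose to the first SBM before the next dose, with section 4's 24-hour rescue rule applied. In the 7-day median, rank a day with no such SBM as longer than the dosing interval instead of leaving it out. Both parts are needed, for the reason in step 5 of the working.

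In section 4, define a CSBM as an SBM without a sense of incomplete evacuation, so that the 24-hour rule applies explicitly.

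The cost is two definition sentences and some programming. Under 7.2.3 the diary already covers medication status, date and time, residual sensation, picked stool and suppository or enema use, and the SBM count already needs the rescue information. Reported times will lengthen, and some weekly medians will have to be given as more than 24 h.
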